### Data Analysis

Data collected will be entered into Stata 10.1 for cleaning and analysis. Preschool, primary school and LDC environmental data that is categorical in nature will be analyzed using Chi-squared or Fisher's exact tests depending on sample size. Data that is continuous or interval in nature (eg staff ratings, frequency of actions etc) will be analyzed using t-tests if normally distributed or by the Kruskal-Wallis equality-of-populations rank test if non-normally distributed. Analysis of the child behavioral data will be at the school level (school as the Primary Sampling Units, PSUs, using the *svy *commands in Stata) using logistic regression (binary and ordinal), and generalized linear models regression with a Poisson distribution for interval data. Child behavioral data will be adjusted for child age, gender and maternal education (as an indicator of socio-economic status). Analysis of the FDC data will be at the local government area level (as the PSUs). Continuous or interval impact and outcome data will be compared using the Wald test of difference in group means, and data that is categorical or ordinal will be analyzed using logistic regression and the design corrected chi squared statistic. An inductive thematic analysis will be conducted for qualitative data.

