### Kids 'Go for your life' Award Program

The K-GFYL intervention is being implemented in a range of children's settings, including primary (elementary) schools (children aged five to twelve years), pre-school (also known as kindergarten; for children aged three to five years), and the early childhood services family day care (FDC, a home-based child care service for children from birth to twelve years) and long day care (LDC, centre-based care for children aged from birth to five years). The K-GFYL program includes support and professional development for staff within those settings to make policy and practice changes that promote healthy eating and physical activity for children and their families [13]. The key obesity-related behaviors targeted are: increasing fruit, vegetable and water consumption; reducing consumption of foods high in fat, salt and sugar and sweet drinks; increasing participation in physical activity; reducing sedentary behavior (such as screen time); and increasing active transport [13]. The intervention was designed within a Health Promoting Schools (HPS) framework [14]; which requires a whole of school/service approach to health promotion. K-GFYL is an award-based program and membership is open to all primary and pre-schools, and early childhood services across the state of Victoria, Australia. Once members, the schools and services are supported to implement the program by a state-wide coordination team, a local government coordinator (available in 10 of the 79 local government areas in Victoria) and local community members of the Kids - 'Go for your life' Health Professionals' network. Once the school or service deems it has fully implemented the program and achieved all of the policy and practice requirements, they apply to become 'awarded' as a Kids - 'Go for your life' school or service. The application is reviewed and assessed by the state-wide coordination team and the award conferred if all of the appropriate criteria are met. From that time, they are referred to as a K-GFYL 'awarded' school or service. It is hypothesized that reaching award status increases children's physical activity and healthy eating behaviors through the creation of health promoting environments, capacity-building and community engagement (see Figure 1).

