## Methods/Design

### Evaluation design

When determining the appropriate evaluation design, the research team considered a number of contextual and limiting factors. These included 1) the implementation of the intervention program across the entire State and current high-level recruitment drive; 2) the funding of this evaluation more than 12 months after state-wide implementation began; 3) the requirement for the evaluation data to be available in a short time frame (all data was to be collected within one school term of 12 weeks); and 4) the limited evaluation funding for this large-scale impact and outcome evaluation in all of the settings targeted by the intervention. Taking these factors and the study aims into consideration, a mixed method, cross sectional evaluation design was deemed the most appropriate to determine differences in impact and outcome measures between those settings/services that were K-GFYL members only and those that were K-GFYL awarded. In the school setting, there will be two groups of awarded schools: newly awarded (<12 months) and longer term awarded (≥12 months), to enable an examination of the sustainability of program impacts after the award is conferred.

The K-GFYL intervention design, implementation strategies and materials were also carefully reviewed to determine the best evaluation methods given the constraints already mentioned. A summary of the main intervention activities implemented is provided in Table 1. Consistent with the intervention design, the evaluation design is guided by the socio-ecological framework [15] and accepted best practice for the evaluation of health promotion projects of this kind [16] (see Table 2). The evaluation was therefore also multi-level and the instruments are outlined in Table 2. The evaluation approach varies across settings due to the nature of the setting, data collection costs and accessibility to the setting/service and participants.

**Table 1 T1:** K-GFYL health promotion activities implemented in settings

K-GFYL Program area	Health promotion activity
Water and sweet drinks	Children have access to water throughout the day (water bottles, jugs and fountains)
	Sweet drinks are restricted or not allowed
	Having access to drinking water is reflected in school/service policy
Fruit and Vegetables	Defined periods of time when students/children are encouraged to eat fruit and vegetables only (e.g. Fruit & Veg play lunch, fruit break)

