### Data Collection Instruments

The *School Environment Questionnaire (SEQ) *is a 129 question instrument designed to examine key elements of the school environment. The questionnaire contains items that have been used previously in similar studies we have conducted [17-19] and forms the structure for key informant interviews to capture physical (eg. adequacy of sporting and active play equipment), policy (eg. adoption of nutrition and physical activity policies) and socio-cultural (eg. teachers' role modeling physically active behaviors) elements of the school environment. This structured interview is conducted with 2-3 members of the school staff and also captures information related to the following areas: general demographic information; the food service; school food/nutrition policy(ies); the nutrition environment; school physical activity policy(ies); the physical activity environment; staff knowledge, skills and attitudes; and program implementation activities. Interviews will be completed in a single session approximately 45 minutes in duration and will be conducted by trained research staff. For each question one response will be recorded and where there is disagreement, staff will be asked to discuss the issue until consensus is reached.

The *Child Health Questionnaire *contains 51 items and is designed to capture information from parents/carers of primary school children regarding their child's physical activity, sedentary and nutrition related behaviors. The majority of survey items have previously been used by our research group in similar studies [3,8,17,19,20]

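### Award status is self-selected, but the environment tests take no covariates and the child models adjust for no setting-level factor, so setting-level confounding is left unaddressed

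*Protocol article*

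**What the plan says.** The section on the award program in the protocol article describes how the groups arise. Entry is voluntary: "membership is open to all primary and pre-schools, and early childhood services across the state of Victoria, Australia". When a setting judges itself ready, "they apply to become 'awarded' as a Kids - 'Go for your life' school or service", with "the award conferred if all of the appropriate criteria are met". Nothing is allocated. Under Evaluation design, "a mixed method, cross sectional evaluation design was deemed the most appropriate to determine differences in impact and outcome measures" between member-only and awarded settings.

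The Data Analysis section then fixes the methods:

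- Environment data: "Preschool, primary school and LDC environmental data that is categorical in nature will be analyzed using Chi-squared or Fisher's exact tests". Continuous items get a t-test or a Kruskal-Wallis test.
- Child data: "Child behavioral data will be adjusted for child age, gender and maternal education", the last as a socio-economic indicator, with school as the primary sampling unit.
- No setting-level covariate is named for any analysis, including family day care.

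The Sampling section draws primary schools at random within strata, restricts them to Government schools, and takes as members only schools that joined less than three months earlier, in order to widen the contrast between groups.

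**The concern.** Settings that have applied for and gained an award may differ from recent joiners in ways that came before the award: how disadvantaged the area is, whether it is metropolitan or rural, how large the setting is. Each could affect both reaching the award and the outcome. Random sampling within strata makes each stratum representative of its own kind of school; it does not make the strata alike. Declaring the school as sampling unit corrects standard errors, not bias.

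This matters because of how the results will be read. The award program section hypothesizes that reaching the award raises children's healthy behaviors, and the Discussion promises evidence on the program's impacts to inform policy. The limitations listed in the abstract and Discussion cover the absent non-program control group, time, funding and monitoring data. They do not mention self-selection into the award.

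**Working it through.** **What the existing controls cover**

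- Government-school restriction: removes sector differences, among primary schools only.
- Maternal education: removes part of the socio-economic confounding, in child models only.
- Preschool and long day care environment tests: neither control applies.
- Primary-school environment tests: only the sector restriction applies.

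**The plan's own figure.** The detectable difference is (1.960 + 0.842) × SD × √[DEFF × (1/n₁ + 1/n₂)], two-sided 5% (sidedness assumed), 80% power. With SD 1.14, DEFF 1.98, and 30 v 30 schools of 20 children (600 v 600):

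2.802 × 1.14 × √(1.98 × 2/600) = 0.259, against the stated 0.26.

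The figure reproduces. It covers sampling error only and assumes no bias.

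**Sensitivity of the child comparison to bias.** The article gives no bias size, so the values below are assumptions. With no true effect and bias b, the rejection probability is 1 − Φ(1.96 − b/SE) + Φ(−1.96 − b/SE). With ICC 0.02 and 20-30 children per school, DEFF = 1 + (m − 1) × 0.02 = 1.38 to 1.58.

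- 30 v 30 schools, 20 children each: SE = 1.14 × √(1.38 × 2/600) = 0.077
- 30 v 50 schools, 30 children each: SE = 1.14 × √[1.58 × (1/900 + 1/1500)] = 0.060

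| Assumed bias (serves) | Rejection probability across these two cases |
|---|---|
| 0 | 5% |
| 0.05 | 10-13% |
| 0.10 | 25-38% |
| 0.20 | 74-91% |

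With the article's upper design effect of 1.98 the SEs are 0.093 and 0.068, and a bias of 0.10 gives 19-32%.

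**Staff ratings, preschools and long day care.** 20 v 30 services, SD 1.3: SE = 1.3 × √(1/20 + 1/30) = 0.375. An assumed bias of 0.25 unit gives 10%; 0.5 unit gives 27%.

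**Which benchmark fits a yes/no item.** At 50% prevalence (assumed):

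- Child item, 30 v 30 schools × 25 children, DEFF 1.98: 2.802 × √(0.25 × 1.98 × 2/750) = 10.2 points, in line with the stated 10
- Environment item, one observation per school, 30 v 50: 2.802 × √[0.25 × (1/30 + 1/50)] = 32 points
- Environment item, 20 v 30 services: 2.802 × √[0.25 × (1/20 + 1/30)] = 40 points, as stated

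The 10-point figure therefore belongs to child data and is no yardstick for environment items.

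**The case against.** **Aim 1 asks only about association, and crude tests answer that.** This stands as far as description goes: the tests are valid for whether the groups differ. It does not cover the reading as impact that the article itself gives.

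**The award is conferred on policy and practice criteria, so the Aim 1 exposure is partly defined by its outcome.** This stands. No covariate adjustment turns the Aim 1 contrast into an effect of the award, which is why the limitation has to be stated as well.

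**A condensed article may leave adjusted analyses to a fuller plan.** Possible, but here the article names the tests and lists the covariates. The point is about what it fixes.

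Several stronger readings are tempting and are not supported:

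- *The bias could equal the whole effect the study is sized for, in favour of the award.* Suppose a confounder 20-40 points more common among awarded settings raises a practice by 15-25 points. The bias is then 0.20 × 0.15 = 3 to 0.40 × 0.25 = 10 points. These inputs have no source in the article. Set against the right benchmarks, 10 points is 31% of 32 and 25% of 40. Nothing in the article fixes the direction.
- *The local coordinator is the obvious confounder.* The article does mention "a local government coordinator (available in 10 of the 79 local government areas in Victoria", but as one of the ways members are supported. That makes it program delivery, and adjusting for it could remove part of the program's own effect.
- *Using local government area as sampling unit for family day care but not elsewhere is inconsistent.* That choice concerns variance, not confounding, and primary schools are sampled as schools.
- *Confounding passes unhindered into both aims.* The sector restriction and maternal education remove some of it.

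**Conclusion.** The point holds in a limited form. Exposure is self-selected, the comparison is cross-sectional, the environment tests admit no covariates, and the child models contain no setting-level factor. Confounding by area disadvantage, location and size is thus not addressed, least of all for the preschool and long day care environments. Its size and direction are unknown. The rejection rates show only that a modest bias would matter: 0.10 serves is under half of the detectable 0.26. They rest on assumed bias values, a true effect of zero, SD 1.14 and ICC 0.02. This is a worthwhile and inexpensive improvement to the analysis. It is not evidence that the planned tests are invalid or that the results will favour the award.

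**What to change.** - For a short list of key environment outcomes, report linear or logistic regression (penalised where cells are sparse) beside the crude tests, adjusted for two or three covariates that precede the award: area disadvantage, metropolitan/rural location and enrolment size.
- Add the same covariates to the primary-school child models.
- Treat presence of a local coordinator as a sensitivity analysis only, because it is part of program delivery.
- State as limits on causal interpretation that settings select themselves into the award and that the award criteria overlap the Aim 1 outcomes.

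Cost: analysis wording and a small data task. Area disadvantage and location follow from the setting's address. The School Environment Questionnaire collects "general demographic information", but the article does not say that enrolment is included, so it may have to come from records. With 50 to 80 settings only a few covariates can be carried and some precision is lost. Residual confounding remains, including any difference between recent joiners and schools that have already completed the program.

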### Consenting and Ethics

All data is to be collected from adult participants, who will be asked to provide written informed consent prior to data collection. School principals, preschool directors and service managers will also provide consent before staff and parents are invited to participate. Approval for this study has been obtained from the University of Melbourne Human Research Ethics Committee (HREC #0828812) and the Department of Education and Early Childhood Development.

## Discussion

As a result of government policy and funding, the K-GFYL intervention was developed and implemented in Victoria, Australia. The award-based program utilizes socio-ecological and health promoting schools approaches to prevent childhood obesity across the entire community by targeting a range of children's settings and services. Currently there is no evidence available about the efficacy or effectiveness of such an approach for childhood obesity prevention, although there is a growing body of evidence that community-based approaches can be effective. Evaluations of community-based health promotion programs are challenging [16], however added challenges for this evaluation are the delayed and limited funding of this phase of the evaluation (relative to the start of the intervention and the collection of process evaluation and pilot data), the large-scale, state-wide implementation of the program (and therefore lack of available control group), the limited time available for data collection, and the lack of any local level population monitoring data (which limits our ability to determine the impact of the intervention of child anthropometric and weight status outcomes).

Despite these constraints and limitations we have planned a comprehensive evaluation that will generate valuable evidence about the impacts of the K-GFYL intervention in schools and early childhood services. This new evidence can inform future public health policies and the development and implementation of health promotion programs to prevent childhood obesity at a population level.
